### Process evaluation of the intervention

To understand patient experiences and attitudes about the intervention (prescribed water intake), a process evaluation substudy will be conducted, using methods previously described.^45^ Measures assessed will include the frequency, timing and difficulties experienced with intervention and the intervention tools (telephone coaching, USG, SMS, water bottles, water and diet guidebook, website). The data will be collected using a questionnaire during study visits, and a semi-structured telephone interview will be conducted in a minimum of 30 intervention group participants following the final study visit. Thematic analysis will identify key facilitators and barriers to intervention uptake.

### Economic evaluation

A trial-based economic evaluation, from the perspective of the health funder will be conducted. Information on quality-adjusted life years (QALYs) will be collected using the short form 6D calculated from the KDQOL (SF-1.3). Self-reported healthcare utilisation and costs will be collected at routine clinic visits and intervention costs (staff, training, capital costs and consumables) will also be included. Using the mean costs and the mean health outcomes in each trial arm, the incremental costs per QALY of the intervention group compared with the control group will be calculated; results will be plotted on a cost-effectiveness plane. Bootstrapping will be used to estimate a distribution around costs and health outcomes, and to calculate the CIs around the incremental cost-effectiveness ratios. One-way and multiway sensitivity analyses will be conducted around key variables. A cost-effectiveness acceptability curve will be plotted to provide information about the probability that the intervention is cost-effective, given willingness to pay for each additional QALY gained.

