### Study visits

*Screening visit (up to month 1.5)*. If a patient meets all inclusion criteria and no exclusion criteria, he or she will be enrolled in the trial. At this visit, participants will have their medical and ADPKD history reviewed, usual fluid intake and kidney pain (using the Halt Progression of Polycystic Kidney Disease (HALT-PKD) study group questionnaire)^29^ assessed. A venous blood sample and spot urine sample will also be collected for DNA analysis and biomarker assessment (see below). Due to the cost and time required to perform genetic testing, the effect of *PKD* mutation type on trial outcomes will be assessed retrospectively. Participants will then be asked to have two 24 hours urine collections and blood tests (for testing baseline electrolytes, eGFR and osmolality) as an outpatient at a local pathology collection centre, and a renal MRI (to assess baseline TKV) will be performed at an external radiology facility. The period from screening to randomisation visits (up to 12 weeks) will serve as the run-in period to confirm the participant’s willingness to adhere to study procedures.*Randomisation and baseline visit (month 0)*. Follow-up medical and ADPKD histories will be taken and venous blood and urine samples will be collected at this visit. Participants randomised to the control group will continue with their usual (ad libitum) water intake and standard treatment. Participants in the intervention group will be advised to adjust their daily water intake for the next 36 months, in addition to continuation of their standard treatment, and be provided with specific instructions, described in the section under *study intervention (group B)*.*Treatment period*. The 3-year treatment period includes repeat outpatient blood and 24 hours urine collections (at 3-monthly intervals in year 1 and 6-monthly in years 2–3), progress MRI scans (at 18 and 36 months) and visits to the study centre every 6 months.*Follow-up study visits (months 6, 12, 18, 24, 30 and 36)*. Progress medical and ADPKD histories and further collections of venous blood and urine will be undertaken at follow-up study visits. Study staff will record answers to specific questions on adverse events (AEs) and kidney pain (using the HALT-PKD questionnaire). In both groups, quality of life will be assessed 6-monthly (month 0, 6, 12, 18, 24, 30 and 36) and usual fluid intake will be assessed annually (month 0, 12, 24 and 36). At the final treatment visit at month 36, intervention group participants will be advised that they may return to their previous ad libitum water intake.*Post-treatment study visit*. This will occur at month 37 for all participants.

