
### Randomisation procedure

Participants will be randomly allocated in a 1:1 ratio (in permutated blocks of 4) to the control group or the intervention group, stratified by baseline eGFR (<60 or ≥60 mL/min/1.73 m^2^). Randomisation and concealed allocation will be performed with a secure, web-based randomisation service (Randomize.net). The trial statisticians have generated a validated randomisation list.

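### Bootstrap confidence intervals on the ICER become unreadable if the QALY difference is close to zero; incremental net benefit with adjustment for baseline utility would be safer

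*Protocol article*

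**What the plan says.** The Economic evaluation section describes a trial-based cost-utility analysis with QALYs from the SF-6D, which is derived from the KDQOL questionnaire. The incremental cost per QALY is obtained "Using the mean costs and the mean health outcomes in each trial arm". Bootstrapping is to give a distribution around costs and outcomes and is also used "to calculate the CIs around the incremental cost-effectiveness ratios". Two displays are planned alongside: "results will be plotted on a cost-effectiveness plane", and "A cost-effectiveness acceptability curve will be plotted to provide information about the probability that the intervention is cost-effective" over willingness-to-pay values.

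The section does not say how the bootstrap interval is built, does not mention net benefit, and neither states nor excludes adjustment for baseline utility. Under Study visits, quality of life is measured in both groups every 6 months from month 0 to month 36, so a baseline SF-6D will exist. Randomisation is 1:1, stratified by eGFR below or at least 60.

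**The concern.** The ICER is a ratio whose denominator can change sign. A negative value can mean cheaper and better, or dearer and worse. As the QALY difference approaches zero, the ratio runs to plus or minus infinity. Ranking replicates by their ICER and cutting off the tails then orders results that have no common meaning.

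A small QALY difference is a reasonable possibility here. The Primary end point section says that dialysis-dependent failure takes decades to develop, and the trial is sized on ht-TKV, not on QALYs. What is at stake is whether the one interval named for the cost-effectiveness result can be interpreted.

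A second, lesser matter is precision. A QALY total built from 6-monthly utilities correlates strongly with baseline utility, so a comparison of arm means without that covariate is noisier than it need be and is exposed to chance imbalance.

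**Working it through.** **Plan's own figures.** The Economic evaluation section states none. The only figure carried over is the number of participants: 90 per arm less 15% dropout gives 90 × 0.85 = 76.5, taken as 76 per arm. The power statement in Sample size calculation reproduces (75 per arm, difference 1.9, SD 3.8: 86.5%, against 87% stated) and is not in dispute.

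**Assumed inputs.** The QALY difference (dQ), the cost difference (dC), their SEs, the utility SD and the within-person correlation are all assumptions.

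**1. Ratio against net benefit.** Take dC = A$1,500 (SE 500) and SE(dQ) = 0.03, independent and normal.
- Share of replicates with dQ < 0: Φ(−dQ/0.03).
- Net benefit at A$50,000 per QALY: 50,000 × dQ − 1,500. Its SE is √[(50,000 × 0.03)² + 500²] = √2,500,000 = 1,581.
- Net-benefit CI: mean ± 1.96 × 1,581 = mean ± 3,099.
- ICER limits: simulated 2.5th and 97.5th percentiles of dC/dQ.

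| dQ | dQ < 0 | ICER percentile limits (A$/QALY) | Net benefit, 95% CI (A$) |
|---|---|---|---|
| 0.02 | 25% | about −620,000 to +655,000 | −500 (−3,600 to +2,600) |
| 0.05 | 5% | about −144,000 to +241,000 | +1,000 (−2,100 to +4,100) |
| 0.10 | <0.1% | about +4,800 to +40,900 | +3,500 (+400 to +6,600) |

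Repeated simulation moves the limits in the first row by some A$10,000.

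**2. Second set of assumptions.** With 76 per arm, QALY SD 0.3, cost SD 4,000 and dC = 1,000, the ICER limits are about −311,000 to +306,000 at dQ 0.02, −201,000 to +219,000 at 0.05, −7,500 to +69,000 at 0.10 and −1,400 to +14,400 at 0.20. The pattern is the same. At 0.20 the negative lower limit is readable, because practically no replicate has dQ < 0 and a negative ratio can then only mean a saving.

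**3. How often the sign changes.** Over utility SDs of 0.08–0.15 and within-person correlations of 0.5–0.8, with 76 per arm, the share of replicates with dQ < 0 is 50% at a difference of 0, 25–38% at 0.02, 4.5–23% at 0.05 and 0–7% at 0.10.

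**4. Baseline adjustment.** The QALY is the trapezium sum over seven visits, with weights 0.25, five of 0.5, and 0.25. The weights sum to 3 and their squares to 1.375. With utility SD s and constant correlation ρ:
- Var(QALY) = s²[1.375(1 − ρ) + 9ρ]
- slope on baseline b = 0.25(1 − ρ) + 3ρ
- correlation with baseline r = b·s/SD(QALY)
- SE(dQ) = SD(QALY) × √(2/76); adjusted SE = SE(dQ) × √(1 − r²)

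For s = 0.12:

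| ρ | SD(QALY) | b | r | SE unadjusted | SE adjusted |
|---|---|---|---|---|---|
| 0.5 | 0.273 | 1.625 | 0.71 | 0.044 | 0.031 |
| 0.8 | 0.328 | 2.45 | 0.90 | 0.053 | 0.024 |

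One SE of chance imbalance in baseline utility is 0.12 × √(2/76) = 0.0195. It shifts the unadjusted dQ by 1.625 × 0.0195 = 0.032 to 2.45 × 0.0195 = 0.048 QALY.

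**The case against.** The strongest reply is that the same section already provides what a decision-maker needs. The plane shows which quadrants the replicates occupy. The acceptability curve is the probability that net benefit exceeds zero at each willingness-to-pay value; in the first example it would read Φ(−500/1,581), about 38%, at A$50,000. This stands, and it confines the flaw to one reported summary. It does not rescue that summary: the curve gives a probability, and the only interval named for the cost-effectiveness result is the one on the ratio.

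The article also does not say that the interval is a percentile interval. That stands too. The limits above show what the simplest construction would give, not what the authors have committed to.

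Four stronger readings are tempting but not supported.
- **That the whole economic evaluation is uninterpretable.** The plane and curve remain valid across quadrants.
- **That the plan commits to unadjusted means.** Arm means may be adjusted means, and a condensed article commonly leaves that detail to a fuller plan. Adjustment is therefore offered as an improvement and its absence is not charged as an error.
- **That baseline imbalance biases the QALY comparison.** Under randomisation any imbalance is due to chance. Nor does it carry over in full: multiplying it by 3 years assumes complete persistence, whereas the slopes above are 1.6 to 2.5.
- **That the interval undermines the remark on value for money in Outcomes and significance.** That remark follows a discussion of delayed kidney failure and savings on its treatment, not the 3-year within-trial ICER.

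**Conclusion.** The point holds in a narrow form. The article names a CI on the ICER, and a percentile-type interval on that ratio loses its meaning if the replicates cross a zero QALY difference. Whether they will cross is unknown. Under the assumptions used it is likely at a difference of 0.02, appreciable at 0.05 and largely absent at 0.10. Net benefit stays readable in every case, and the method has to be fixed before the difference is known.

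Adjustment for month-0 SF-6D would cut the SE of the QALY difference from about 0.044–0.053 to 0.024–0.031, if the utility SD is 0.12, the within-person correlation is 0.5–0.8 and 76 per arm are analysed. That is a gain in precision and protection against chance imbalance. The importance is minor: the primary end point, the clinical end points, the sample size and safety monitoring are untouched.

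**What to change.** Replace the ICER confidence interval with the 95% CI of incremental net monetary benefit at stated willingness-to-pay values, taken from the same bootstrap with each participant's costs and QALYs resampled together. Keep the ICER point estimate, the cost-effectiveness plane and the acceptability curve.

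State that the QALY difference is estimated by regression on arm, month-0 SF-6D and the eGFR stratum used at randomisation, refitted within each bootstrap replicate.

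The cost is a change of wording in the economic analysis. Every variable needed is already scheduled for collection, and no visit, measurement or sample size changes.

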### Comparison of prescribed water intake with pharmacological suppression of AVP

It would be important for consumers, policy-makers and other stakeholders to be informed of the direct comparative treatment effects of suppressing the AVP pathway in ADPKD using prescribed water intake or by pharmacological inhibition with a vasopressin receptor antagonist. In this regard, the addition of a third trial arm to compare prescribed water intake with open-label treatment with a vasopressin type 2 receptor antagonist (such as tolvaptan, Otsuka Pharmaceuticals; or Lixivaptan, Palladio Biosciences) in the PREVENT-ADPKD study was considered. However, the cost of study drug was prohibitive for government grant funding (~$A15 million assuming treatment with tolvaptan at up to 90/30 mg dosage for n=90 participants for 3 years), and commercial sponsorship has not been achieved. Therefore, the investigators will conduct a modelled economic evaluation versus tolvaptan, using trial costs and outcomes, supplemented with best available published evidence to consider costs and outcomes over a longer time horizon to account for future benefits in terms of delayed commencement of dialysis, quality of life and life expectancy. One-way and multiway sensitivity analyses will be conducted around key variables and a probabilistic sensitivity analysis will estimate uncertainty in all parameters.

### Data and safety monitoring board

Prescribed fluid intake is considered a safe treatment. The risk of an SAE related to hyponatraemia is expected to be very low in the study population (<1:100 000), however, to mitigate this, serum sodium concentrations will be monitored regularly throughout the trial. An independent data monitoring safety board (DSMB) has been appointed to monitor the safety and conduct of this trial. Specific aspects that will be reviewed include recruitment rate and losses to follow-up, data quality, compliance with the protocol by participants and investigators, evidence for treatment harm (treatment group differences in SAEs), protocol modifications and continuing appropriates of participant information. The DSMB Charter was ratified in October 2016 and the first DSMB meeting occurred in December 2016.

### Trial monitoring

The monitoring of the trial will be performed independently by the Australasian Kidney Trials Network using a combination of remote-monitoring tools and site visits.

### Study recruitment, retention and study limitations

As discussed earlier, to achieve the target recruitment and maintain retention, multiple recruitment strategies including presentations to local nephrologists, media advertisement and engagement of multiple sites for participants’ convenience to attend study visits will be performed. The individualised nature of the study treatment and regular direct participant contact are key to the retention of participants.^46^ There are no competing studies in ADPKD in the region of the study centres, and regulatory approval of tolvaptan for use in ADPKD has been attained in Europe, Canada and Japan, but not in Australia and the USA, and therefore will not affect recruitment.^47^

The study intervention (prescribed fluid intake) is reliant on the behavioural change to drinking habits of the participant to reach 24 hours urine osmolality ≤270 mOsmol/L. The tailored intervention with a variety of supporting tools as described under *study intervention (group B)* adopts a similar model to other successful long-term behaviour change interventions.^37 48^ However, due to the nature of the western diet, adherence to the trial intervention (both prescribed water intake and limitation of dietary salt and protein restriction) can be difficult even with intensive dietary counselling. Progress results from 24 hours urine volume, osmolality and sodium will be monitored to assess compliance of group B participants to the trial intervention. Additionally, bias and contamination could be introduced by the patient’s expectations and prior knowledge of the hypothesised role of fluid intake in ADPKD, as discussed earlier. Finally, another limitation of the study is that renal function will be estimated by the CKD-EPI equation and it is known that this may not reliably predict longitudinal changes in patients with ADPKD,^49^ which is one of the principal reasons why TKV has been used as the primary outcome measure.

### Proposed timeline and current status of the trial

The study has been in the development phase from 2012 to 2015, and trial recruitment commenced on 9 December 2015 (see table 3). In 2016, the model of a mobile research team was implemented and the active study centres included Westmead, Nepean and Norwest Private Hospitals in Western Sydney and Gosford Renal Research on the NSW Central Coast. In 2017, additional study centres commenced, and as of July 2017, 75% of the intended recruitment has been completed and 100% recruitment is anticipated by the end of 2017.

**Table 3 T3:** Proposed timeline of the PREVENT-ADPKD trial

Year	Milestone (*italics denote milestone has been completed*)
2012–2015	*Study protocol developed (V.4); Australian and New Zealand Clinical Trial registration; lead-site ethics committee approval; trial endorsed by AKTN; data and biostatistical management plan developed; DSMB appointed; randomisation list and electronic case report forms finalised; recruitment at Westmead Hospital started; intervention group supporting tools developed*
2016	*Commenced recruitment at Norwest Private Hospital, Nepean Hospital and Gosford Renal Research* *50% planned recruitment completed*
2017	*Commence recruitment at other Australian sites* *75% recruitment completed in July 2017* Plan to complete recruitment at the end of 2017
2018–2019	Follow-up of study participants
2020–2021	Last participant follow-up Study close-out, data analysis; report key findings

AKTN, Australasian Kidney Trials Network; DSMB, Data and Safety Monitoring Board.

### Outcomes and significance

This trial will determine if fluid intake prescribed to maintain isotonic urine (implemented by coaching, SMS text reminders and self-monitoring of USG by dipstick) reduces the progression of TKV in CKD stages 1–3 due to ADPKD. While a negative result of a properly performed study will be significant in that it will settle the controversy regarding fluid intake in ADPKD, a positive study result will provide an inexpensive, widely generalisable and safe approach to slow renal cyst growth, and one that could be easily taken up in clinical practice and well-tolerated by consumers.^50^ In the best-case scenario, if prescribed fluid intake is found to reduce the annualised rate of increase in TKV by 50%, the development of ESKD could be delayed by 6.5 years and life expectancy extended by 2.6 years,^51^ at a negligible cost over standard treatment, but resulting in considerable cost savings for future treatments of ESKD. Even at lower efficacy this treatment option will be extremely good value for money and this is of vital importance in low-income countries where access to novel drugs and chronic dialysis are restricted due to lack of affordability and availability. However, if the hypothesis is proven, the largest impact will be in children and at-risk individuals with ADPKD (where its introduction in early life could potentially prevent the onset of ESKD).

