**Methods and analysis:**

A multicentre, prospective, parallel-group, open-label, randomised controlled trial will be conducted. Patients with ADPKD (n=180; age ≤65 years, estimated glomerular filtration rate (eGFR) ≥30 mL/min/1.73 m^2^) will be randomised (1:1) to either the control (standard treatment+usual fluid intake) or intervention (standard treatment+prescribed fluid intake) group. Participants in the intervention arm will be prescribed an individualised daily fluid intake to reduce urine osmolality to ≤270 mOsmol/kg, and supported with structured clinic and telephonic dietetic review, self-monitoring of urine-specific gravity, short message service text reminders and internet-based tools. All participants will have 6-monthly follow-up visits, and ht-TKV will be measured by MRI at 0, 18 and 36 months. The primary end point is the annual rate of change in ht-TKV as determined by serial renal MRI in control vs intervention groups, from baseline to 3 years. The secondary end points are differences between the two groups in systemic AVP activity, renal disease (eGFR, blood pressure, renal pain), patient adherence, acceptability and safety.

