Total solutes (urine osmolality×urine vol (mL)) is the mean derived from two 24 hours urine samples collected between the screening visit and the randomisation/baseline visit.*Dietary counselling*. A high dietary solute load (due to high salt and protein intakes) requires a higher fluid intake to maintain urine dilution.^11^ Participants will be educated about the importance of dietary solute intake in determining obligatory urine volume (ie, the minimum urine volume required to excrete the daily solute load).^32^ The study dietitian will take a detailed diet history and provide tailored dietary advice to enable participants to achieve and maintain a moderate protein intake (0.75–1.0 g/kg/day) and limit sodium intake to 80–100 mmol/day.^19^ If the calculated prescription is >3 L/day, the participant will be advised to gradually increase fluid intake until target urine osmolality is reached and focus on reducing dietary solutes to reduce the risk of hyponatraemia.*Review of lifestyle and environmental factors*. The participant’s lifestyle, personal preferences and occupation will be recorded and reviewed when providing individualised techniques for promoting adherence to fluid intake. Participants will be provided with 3×1 L reusable water bottles to help keep track of their fluid intake, and will be encouraged to drink evenly throughout the day and replenish with each episode of nocturia.*Self-monitoring of fluid intake and treatment efficacy*. Aids have been developed to assist participants with self-monitoring, including a paper-based diary or web-based/smartphone compatible tool to self-monitor fluid intake, and urine dipsticks will be provided to record urine-specific gravity (USG). Participants will be shown how to read their USG and will be asked to test it during the late afternoon (16:00–20:00 hours) at least once daily in the first 2 weeks of the study, at least twice weekly for the first 6 months and then at least monthly for the duration of the study. An USG of ≤1.010 indicates a spot urine osmolality of ≤270 mmol/L, meaning that fluid intake in the past few hours has been adequate. Participants will also be briefed on receiving and responding to short message service (SMS) text messages (or emails if they do not own a mobile phone) requesting the results of a late afternoon USG measurement (see below), as well as on the schedule of telephone calls (see below).*Scheduled telephone calls and follow-up study visits*. Participants in the intervention group will be contacted by telephone (at weeks 1, 3 and 6, then monthly in year 1, and 3-monthly for years 2–3) and reviewed face-to-face at all study visits by the Study Dietitian to assess compliance with fluid intake, discuss USG results, ensure that blood and urine samples are collected and to record any AEs and new medications commenced. If necessary, the fluid prescription will be adjusted depending on the results of progress 24 hours urine osmolality and USG. The study dietitian will monitor compliance with protein and sodium recommendations using 24 hours recalls at all study visits.*Response to SMS text messages*. To provide a quantitative measure of adherence, participants in the intervention group will be required to reply (within 12 hours) to an SMS message requesting the results of a late afternoon USG. The SMS message will be delivered randomly twice a week in months 0–6, then monthly for the duration of the study.*Rationale for the intervention*. Previous trials in patients with recurrent nephrolithiasis in Italy and Israel have shown that a long-term increase in fluid intake can be achieved with targeted education provided at clinic visits alone^33 34^ but, for the current study in Australia, telephone coaching by a dietitian and the above tools are included to boost compliance and continued participation.^35^ A systematic review revealed that self-monitoring of USG is a critical tool to enhance the implementation of increased fluid intake in clinical trials.^36^ SMS texting is a method preferred by consumers in health interventions.^37^

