### Sample size calculation

In longitudinal data from the CRISP-II cohort, the average rate of increase in ht-TKV was 5.5% per year (SD, 3.8% per year; n=201; 8-year follow-up). Preclinical and clinical studies using pharmacological inhibition or adequate hydration to inhibit ADH-mediated cyst growth resulted in similar treatment efficacy of ~50% lesser increase in kidney volume.^10^ In this trial, a more modest (but still clinically important) treatment effect of 35% is nominated. Using these assumptions, a total sample size of 150 will have 87% power to detect a difference in ht-TKV of 1.9% per year, using a two-sided test and a 0.05 level of significance. Taking into account the possibility of 15% dropouts, our aim is to include 180 participants (n=90 per arm).

The estimation of dropouts was based on experience from previous clinical trials in ADPKD. Furthermore, it was suspected that there would be significant interest for participants to remain in this study due to the low risk of AEs with the intervention; as well as the strong interest and motivation expressed by patients with PKD at the study centres, in part due to genetic nature of the disease and the paucity of opportunities for clinical research in PKD in the past. In reality, however, the exact proportion of subjects that dropout and/or withdraw from the intervention (protocol deviation) will not be known until the trial has concluded, and is a secondary outcome measure to assess the efficacy of the intervention.

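### The conclusions announced in advance exceed the design: a non-significant result need not settle the fluid question, and a positive one would support the fluid-plus-diet package, not fluid alone

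*Protocol article*

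**What the plan says.** **On a null result.** The section Outcomes and significance states, without condition: "While a negative result of a properly performed study will be significant in that it will settle the controversy regarding fluid intake in ADPKD". The Sample size calculation states that "a total sample size of 150 will have 87% power to detect a difference in ht-TKV of 1.9% per year", with a two-sided 5% test, and that "a more modest (but still clinically important) treatment effect of 35% is nominated". No equivalence or futility margin is given. The controversy, as the Introduction describes it, includes possible harm: a small 12-month cohort study pointed to faster cyst growth with more fluid.

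**On a positive result.** The abstract labels the active arm the "intervention (standard treatment+prescribed fluid intake) group". Outcomes and significance likewise speaks of fluid intake, and lists coaching, text reminders and urine-specific gravity monitoring as the means of delivery, without diet. The section Study intervention (group B) adds tailored dietary advice to "maintain a moderate protein intake (0.75–1.0 g/kg/day) and limit sodium intake to 80–100 mmol/day", with diet recalls at all study visits. The section on recruitment, retention and limitations then counts salt and protein limitation as part of the trial intervention. Under Study visits and Standard treatment, controls keep their usual water intake and their nephrologist's standard care; no trial dietary counselling is described for them.

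**The concern.** Both sentences concern what may be concluded, so they matter most when the result is in.

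- Failing to reject in a superiority trial does not show absence of benefit or harm. What a null result settles depends on which effects its confidence interval excludes, and the article does not make the conclusion depend on that. The protocol itself names poor adherence and contamination as risks, and either could produce a null result without telling us about efficacy.
- If the arms differ in solute counselling and coaching as well as in fluid, a difference in kidney growth cannot be assigned to water alone. The protocol links the two components: the prescribed volume is calculated from solute load, and participants with a high calculated volume are told to concentrate on reducing dietary solutes.

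The question could be closed on effects the trial could not exclude, or a package effect could be reported as an effect of water.

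**Working it through.** **Inputs** (Sample size calculation): "the average rate of increase in ht-TKV was 5.5% per year (SD, 3.8% per year; n=201; 8-year follow-up"; 35% effect; 150 evaluable at 1:1, so 75 per arm; two-sided alpha 0.05.

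**1. Reproduce the stated power.**
- SE of the difference = 3.8 × √(2/75) = 0.62% per year.
- 35% of 5.5 = 1.925, stated as 1.9.
- Normal approximation: power is 86.5% at 1.9 and 87.3% at 1.925 (noncentral t: 86.0% and 86.9%). The stated 87% reproduces, and the sample size is sound for its target.

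**2. Width of the interval.**
- 1.96 × 0.62 = 1.22% per year (1.23 with the t quantile).
- 1.22 / 5.5 = 22% of the control growth rate.

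**3. What a non-significant result would exclude.**

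| Observed benefit (% per year) | 95% CI | Upper limit as % of 5.5 | Excludes 1.9? |
|---|---|---|---|
| 0 | −1.22 to 1.22 | 22% | yes |
| 0.5 | −0.72 to 1.72 | 31% | yes |
| 0.8 | −0.42 to 2.02 | 37% | no |
| 1.0 | −0.22 to 2.22 | 40% | no |

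The interval still contains 1.9 once the estimate exceeds 1.9 − 1.22 = 0.68, and the test is non-significant up to 1.22. Estimates of about 0.7 to 1.2% per year are therefore non-significant yet compatible with the design effect.

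**4. Power for smaller true effects** (75 per arm, normal approximation): 60% for a 25% reduction (1.375), 43% for 20% (1.1) and 14% for 10% (0.55).

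**5. Sensitivity.** The SD comes from an 8-year cohort; a range of ±20% is my assumption.

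| Case | Half-width | As % of 5.5 | Non-significant band still containing 1.9 |
|---|---|---|---|
| SD 3.04, 75 per arm | 0.97 | 18% | 0.93 to 0.97 |
| SD 3.8, 75 per arm | 1.22 | 22% | 0.68 to 1.22 |
| SD 3.8, 90 per arm | 1.11 | 20% | 0.79 to 1.11 |
| SD 4.56, 75 per arm | 1.46 | 27% | 0.44 to 1.46 |

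The planned baseline-adjusted analysis of log ht-TKV may change these widths somewhat.

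**6. The contrast between arms.** No arithmetic applies. The abstract and Outcomes and significance describe a contrast in fluid. Study intervention (group B) and the limitations section describe fluid plus sodium and protein limitation. These are two different descriptions of the same comparison.

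**The case against.** **A null result could be quite informative.** This stands. An estimate near zero would exclude both the nominated 35% and the 50% best case. If the true effect were zero, the interval would exclude 1.9% per year about 86% of the time. A reader might infer that a null trial could settle nothing; the figures do not support that. The point is only that settlement cannot be assumed before the interval is seen.

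**The article does not say that effects below 35% are worthwhile.** A reader might take "Even at lower efficacy this treatment option will be extremely good value for money" as an admission that it does. The sentence follows a best case of 50%, so it means lower than 50%, which includes 35%. It cannot carry the claim of an internal contradiction.

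**The diet component is disclosed and belongs to the design.** It appears under the intervention heading and among the limitations, and solute load enters the prescription formula. Testing the package is legitimate. What remains is the inconsistent label and the attribution that follows from it.

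**Controls may also receive dietary advice.** A reader might infer that they get none. The text does not establish that, because the dietary content of standard care is not described. What can be said is that the structured trial counselling is described for group B only.

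**These are closing remarks in a journal article, and detail may sit in an analysis plan.** No test or sample size depends on them, and the osmolality comparison is already planned. But the concern is with what the article does state: an unconditional conclusion and a fluid-only label.

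**Conclusion.** The point holds in two limited parts.

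- **Null result.** It cannot be assumed to settle the question. On the planning assumptions the half-width is about 1.2% per year, or about 1.0 to 1.5 over the assumed SD range and 1.1 if all 90 per arm are evaluable. Near zero, the result rules out the 35% and 50% effects but not changes of about 22% in either direction. In the upper part of the non-significant range it does not rule out 35%.
- **Positive result.** It would be valid for prescribed fluid with dietary solute counselling and coaching. It would not identify the contribution of fluid alone.

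The first part assumes that the cohort SD applies to 3-year slopes and that the comparison behaves roughly like an unadjusted one. The second rests on the text as written, with control-arm dietary care undescribed. The fault lies in the interpretive wording and the arm label; the sample size calculation is not in question.

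**What to change.** 1. Replace the sentence on a negative result. State that a non-significant result rules out only effects outside the 95% confidence interval, so a 35% benefit is excluded only if 1.9% per year lies outside it. State that the result will be read beside the achieved between-arm difference in 24-hour urine osmolality, already a secondary end point.
2. Name the comparison the same way throughout: prescribed fluid plus dietary solute counselling and coaching, versus usual fluid intake with standard treatment. Limit the positive conclusion to that package.
3. Report 24-hour urinary sodium and urea by arm. Study measurements already provides for urine electrolytes and urea in both groups at the scheduled collections; the limitations section mentions urinary sodium only for monitoring group B compliance.

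The cost is a more modest claim and one extra table. Treatment, sample size and data collection are unchanged.
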